## Abstract

**Background:**

Persons with inflammatory bowel diseases are at increased risk of developing colorectal cancer and require frequent colonoscopy surveillance. Guidelines recommend taking 30 to 40 non-targeted biopsies throughout the colorectum to detect “invisible” neoplasia in this setting, despite a lack of evidence supporting this practice. We sought to assess the utility of this practice through a randomized controlled trial. We first propose an internal pilot study to assess recruitment potential, protocol adherence and data capture to guide the full trial.

**Methods:**

We have designed a multi-centre, parallel-group, non-inferiority randomized controlled trial to test the utility of non-targeted biopsies as an adjunct to colonoscopy surveillance for neoplasia detection in persons with inflammatory bowel disease involving the colorectum in routine clinical practice. Participants are randomized 1:1, stratified by study site, to either standard of care high-definition white-light colonoscopy with 32 to 40 non-targeted biopsies of non-neoplastic-appearing mucosa along with a sampling of abnormal-appearing mucosa (control group) or modified colonoscopy with targeted sampling alone (intervention group). The primary outcome for the full trial will be the proportion of persons with ≥ 1 neoplastic focus detected during colonoscopy. For the pilot phase, we will assess the feasibility of recruiting a minimum of 15% of the estimated sample size within 1 year, under identical conditions as the full trial, while maintaining ≥ 90–95% rate of protocol adherence and data capture. These participants will contribute data to the full trial. The trial is being conducted at 12 centres across Canada, with a total sample size of 1952 persons.

**Discussions:**

The trial protocol has been approved by the ethics committees of all participating sites, and the pilot study has received funding through the Canadian Institutes of Health Research (PJT 159607). If feasibility metrics are met during the pilot phase, we will complete the full trial. The trial outcomes will contribute to update the practice guidelines in this area.

**Trial registration:**

ClinicalTrials.gov, NCT04067778.

**Supplementary Information:**

The online version contains supplementary material available at 10.1186/s40814-023-01434-8.

## Background

Inflammatory bowel diseases (IBD), including Crohn’s disease (CD) and ulcerative colitis (UC), are characterized by acute and chronic inflammation of the gastrointestinal tract and extra-intestinal organs and are associated with substantial morbidity related to active disease symptoms, bowel surgery and colorectal cancer (CRC). IBD afflicts more than 0.3% of persons in developed nations, and the incidence is rising in newly industrialized countries [1–3]. CRC is a devastating complication of IBD involving the colorectum, accounting for as much as 15% of IBD-related deaths [4]. Persons with colorectal IBD have a 1.5- to 3-fold higher risk of developing CRC relative to age-matched members of the general population [5–7] and require frequent screening with colonoscopy to detect and treat pre-cancers and early-stage cancers [5–7].

Guidelines have long recommended that screening exams include 33 or more non-targeted (“random”) biopsies throughout the colorectum to screen for “invisible” neoplastic lesions, in addition to targeted biopsies or resection of visible lesions [8–11], based on mathematical modelling in one study showing that ≥ 33 jumbo forceps biopsies are required throughout the colorectum to detect one neoplastic focus with 90% confidence in an individual with pancolitis [12]. The rationale for taking non-targeted biopsies is based on a fear of “invisible” neoplasia (dysplasia) in persons with colorectal IBD, emanating from molecular studies reporting widespread DNA damage in areas of chronic colitis (“field carcinogenesis”) [12–15], as well as reports of high rates of synchronous and metachronous CRC in persons with colorectal IBD who have neoplasia identified during screening colonoscopy [16–25]. Furthermore, neoplasia in IBD can take on unconventional growth patterns, including flatter growth and growth resembling acute and chronic inflammatory changes (nodular, stricturing and ulcerated growth patterns) [26, 27] that could easily evade detection during colonoscopy.

Despite the theoretical value of taking non-targeted biopsies in this setting, there is an absence of controlled data to support this practice. To date, only one small randomized controlled trial (RCT) from Japan has addressed this question and demonstrated the non-inferiority of eliminating non-targeted biopsies [28]. Importantly, most of the aforementioned studies suggesting increased risks of invisible neoplasia were conducted during eras of limited treatment options for IBD, poorer resolution endoscopes (even optical endoscopes) and relative absence of endoscopy practice quality parameters, all of which could have contributed to the challenges in properly identifying neoplasms during colonoscopy. The past two decades have witnessed the introduction of highly effective biologic therapies for treating IBD [29–34], a shift from symptom-based treatment to targeting complete bowel healing [35–40], vast improvements in endoscope technology [41–43] and introduction of numerous endoscopy practice quality standards (bowel preparation quality, cecal intubation rates, colon inspection times and polyp detection rates) [44–47], all of which have likely contributed to reduced rates of CRC and improved detection of subtle and indistinct lesions during colonoscopy in this population [48, 49]. Recent studies have shown that more than 90% of neoplastic lesions are visible using high-definition white-light endoscopy (HD-WLE) [50], that non-targeted biopsies of normal appearing mucosa have an exceedingly low yield for detecting neoplasia (0.1–0.2% of biopsies) [50, 51] and that the rates of synchronous and metachronous cancers in the setting of neoplasia have declined considerably over time [51, 52]. Additionally, the prognostic significance of minute foci of neoplasia detected only through non-targeted biopsies is unclear. These factors have led many experts to question the value of continuing to take widespread non-targeted biopsies for neoplasia screening [51, 53, 54].

On the other side of the argument, several recent large observational studies have reported that non-targeted biopsies continue to identify up to 20% of neoplastic foci in colorectal IBD. While the extent to which non-targeted biopsies in these retrospective reviews were taken from the areas of subtle mucosal abnormality, active inflammation or poor bowel preparation (where the view was obscured), as opposed to normal-appearing mucosa, is uncertain, these reports have nonetheless fueled the debate regarding this practice. Notably, non-targeted biopsies were most useful in individuals with other CRC risk factors in these studies, including primary sclerosing cholangitis, prior colorectal neoplasia, active inflammation and extensive colonic scarring [50, 51, 55].

In a recent survey of Canadian gastroenterologists, 55% of respondents stated that non-targeted biopsies are not an effective method for neoplasia detection in IBD patients; yet, more than 75% of respondents reported that they still routinely carry out this practice [56]. Amongst panellists from the Surveillance for Colorectal Endoscopic Neoplasia Detection and Management in Inflammatory Bowel Disease Patients (SCENIC) international consortium, 45% agreed and 30% disagreed with the practice of performing non-targeted biopsies when using HD-WLE [50]. The variability in physicians’ perceptions regarding this practice may be a combination of the evolving and inconsistent data on this topic, the persistence of this recommendation in guidelines and the absence of definitive evidence refuting the merits of this practice.

In addition to uncertainty regarding its effectiveness, reliance on non-targeted biopsies for neoplasia detection can detract from careful inspection of the colorectum and reduce the likelihood of identifying visible abnormalities [28, 57]. Extensive biopsy sampling may also increase the risk of significant colonic bleeding and bowel perforation, particularly in light of a growing demographic of elderly IBD patients [58] and increasing use of anti-platelet and anti-coagulant agents in society [59, 60]. Moreover, this practice adds 15 to 20 min to colonoscopy time [56, 57], which reduces procedural capacity and increases wait times for other patients. Finally, the specimen processing and pathologist costs associated with obtaining and interpreting 30 to 40 biopsy specimens account for up to 50% of the cost of performing a colonoscopy in this setting [61], placing potentially unnecessary financial strain on the health care system.

These arguments provided a strong impetus to conduct a well-powered RCT to evaluate the utility of non-targeted biopsies as an adjunctive intervention during screening and surveillance colonoscopy in persons with colorectal IBD.

## Study objectives

The primary aims for the pilot phase of the study are to assess recruitment feasibility, protocol adherence and data capture. The overarching study aim is to evaluate whether the practice of taking routine interval non-targeted biopsies could be eliminated from colonoscopy screening and surveillance in persons with colorectal IBD without impacting the overall neoplasia detection rate. Additional aims for the full trial are to assess the impact of eliminating non-targeted biopsies on the rates of visible neoplasia, missed invisible neoplasia, adverse events and future CRC, as well as on procedure time.

## Study eligibility

All adults (≥ 18 years old) with colorectal IBD who are undergoing routine surveillance colonoscopy and meet the following criteria will be included:Minimum 8 years colorectal IBD duration or any duration if concomitant PSCMinimum historical endoscopic or histologic disease extent of proctosigmoiditis (UC) or 1/3 colorectum (CD)At least 50% of colorectum present and meeting the minimum criteria for disease extentIn symptomatic remission at the time of colonoscopy (Harvey-Bradshaw Index < 5 in CD [62] or partial Mayo Score (pMayo) ≤ 2 in UC [63])Colonoscopy being performed using high-definition white-light endoscopyMinimum of 1 year since the last colonoscopy performed for neoplasia surveillanceComplete colorectal examinationGood to excellent bowel preparation after washing (Boston Bowel Preparation Scale score of 2 to 3 in all segments [64])Limited inflammatory activity— ≤ 25% of colorectum affected by moderate-to-severe inflammation (pMayo 2–3 in UC or non-aphthous ulceration in CD) or no more than 50% of colorectum affected by mild inflammation (Mayo 1 in UC or aphthous inflammation in CD)

The following are the exclusion criteria:Unable to provide informed consentHistory of colorectal cancerPrior subtotal or total colectomy (> 50% of colon removed)Undergoing colonoscopy for repeat evaluation of recently identified colorectal neoplasiaUndergoing pancolonic dye spray chromoendoscopy (DCE) or virtual chromoendoscopy (VCE)

## Trial design and conduct

This is a multi-centre, parallel-group, non-inferiority RCT. Participants meeting the eligibility criteria will be randomly allocated to one of the two groups, stratified by study site, using a web-based central randomization scheme coordinated by the Ottawa Methods Centre:Control group—standard of care screening/surveillance colonoscopy, with 32–40 interval non-targeted biopsies of non-neoplastic-appearing mucosa, as well as targeted biopsies or endoscopic resection of suspicious visible mucosal abnormalitiesIntervention group—modified screening/surveillance, with targeted biopsies or endoscopic resection of suspicious visible mucosal abnormalities alone

Randomization will occur intra-procedurally, once all clinical and endoscopic eligibility criteria have been confirmed. Study investigators and/or their trained research assistants will perform the following tasks: (i) assess study eligibility and obtain informed consent from patients; (ii) directly observe the study-related colonoscopy (trained assistant), to confirm intra-procedural eligibility criteria, randomize patients, ensure colonoscopy protocol adherence and obtain procedure-related information pertinent for the trial; (iii) perform medical record review, to collect historical and post-procedural data, including histology of biopsy/resection samples; (iv) conduct a virtual interview with patients a minimum of 2 weeks following the study colonoscopy, to ascertain procedure-related adverse events; (v) record all study-related data in a web-based case report form (developed by the Ottawa Methods Centre); and (vi) facilitate transfer of de-identified physical or electronic slide sets from patients with neoplasia/dysplasia for central adjudication.

## Study outcomes

The following are the pilot phase outcomes (minimum metrics to justify full trial):(i)Randomization of ≥ 15% of full trial sample size (292 participants) within 1 year of study initiation across the participating sites(ii) < 10% rate of major protocol violations, on a per-patient basis(iii) < 5% miss rate for non-essential variables and < 1% for essential variables (group allocation, intra-procedural interventions and neoplasia findings) on a per-patient basis(iv) < 5% loss-to-follow-up (LFU) for the 2-week post-procedural assessment

### Future trial outcomes

The primary outcome is the proportion of persons with ≥ 1 neoplastic focus in the colorectum.

The following are the secondary outcomes:(i)The mean and median number of neoplastic lesions per person(ii)The rate of advanced neoplasia (any of CRC, high-grade neoplasia, large neoplasia (> 2 cm diameter) or multifocal neoplasia (≥ 3 independent neoplastic foci throughout the colorectum))(iii)The neoplasia yield of non-targeted biopsies(iv)The mean and median number of tissue samples per person(v)The mean and median procedure time(vi)Rate of serious adverse events (SAE) within 2 weeks of colonoscopy [69] (hospital admission, bowel perforation, severe rectal bleeding requiring blood transfusion and/or repeat colonoscopy, acute cardiac or respiratory compromise or death)(vii)Proportion of persons referred for colectomy based on neoplastic findings(viii)The mean and median time to the next recommended surveillance examination(ix)Incidence of CRC over 5 years following study colonoscopy (obtained through linkage of patient data to provincial cancer registries or direct patient contact, at least 5 years following study completion)

We will conduct exploratory sub-group analyses of the primary outcome and multiple secondary outcomes based on disease type (CD vs UC), disease duration and prior biologic exposure.

## Study variables

The study case report form, detailing all variables that are being captured as part of this trial, is provided in Additional file 1.

## Sample size calculation

The estimated sample size to assess non-inferiority of the intervention in the full trial is 1952 persons (976 per group), based on a 1-sided significance level of 2.5% and 80% power, assuming neoplasia detection rates of 15% and 14.5% in our control and intervention groups, respectively, and a non-inferiority margin of 5%. Our sample size estimate for the pilot phase (≥ 15% of the study sample size recruited within 1 year of study initiation) is guided by the feasibility of completing the full trial within an acceptable time frame of 5 to 7 years.

Our estimates for neoplasia yield in the 2 groups were guided by pooled analyses of clinical trials and observational cohorts conducted by the SCENIC consortium [50]. The pooled estimate from 4 studies (382 patients) of HD-WLE with non-targeted and targeted sampling was 17%, while the pooled estimate from 7 studies (1289 patients) of DCE (an alternative detection method to non-targeted sampling) was 13.6% [50]. A reasonable estimate for neoplasia detection rate in the control group is thus 15%. The pooled estimates for the proportion of persons diagnosed with neoplasia in non-targeted biopsies alone in these analyses ranged from 1.2% (in studies using DCE) to 1.5% (in studies using HD-WLE). However, we anticipated that these would be overestimates of the difference that would be observed in a present-day RCT, given continued improvements in IBD treatments, endoscope technology and colonoscopy practice quality, as well as a propensity towards closer inspection for visible lesions in the absence of non-targeted biopsies [28, 57]. Therefore, we estimated a 0.5% reduction in the neoplasia detection rate without non-targeted biopsies for this trial.

The proposed non-inferiority margin of 5% is based on a large meta-analysis of 14 surveillance cohort studies in 671 patients with colonic IBD diagnosed with low-grade neoplasia (LGN) by either non-targeted or targeted biopsies, which calculated a pooled rate of progression of LGN to CRC of 0.8% per year [52]. Based on this estimate, if one-third of persons with LGN were missed in our intervention group relative to our reference group (i.e. reduction in absolute neoplasia detection rate from 15 to 10%), it would result in a theoretical 0.04% increased risk per year of CRC in our intervention group or 1 in 500 persons over 5 years. The steering committee and content experts deemed this to be an acceptable upper limit for a reduction in the neoplasia detection rate for the trial, given the potential for reduced procedural risks and costs with avoidance of non-targeted biopsies. This estimate also aligns with the only other RCT on this topic, in which investigators used a non-inferiority margin equivalent to roughly one-third of the baseline neoplasia detection rate [28].

## Data analysis

We will evaluate the pilot study results based on participant recruitment rate, protocol adherence and quality of data capture. Treatment allocation will remain concealed to study investigators following the completion of the pilot phase so as to not influence ongoing study recruitment. We require a minimum of 292 participants (> 15% of the full trial sample) to be recruited within 1 year of trial initiation at each site to deem adequate feasibility of recruitment for the full trial. We will accept up to a 5% rate of major protocol violations, up to a 1% miss rate of major variables and up to a 5% LFU amongst study participants recruited during the pilot phase. If these metrics are met and there are no safety concerns with the study intervention based on the Data and Safety Monitoring Committee (DSMC) review, we will proceed with recruitment to the full trial.

The full trial results will be assessed by per-protocol analysis and intent-to-treat (ITT) analyses. The chi-square test will be used to analyze the differences in binary categorical outcomes, and Student’s *t*-test will be used to analyze the differences in continuous outcomes. Non-inferiority of the primary outcome (proportion of persons with neoplasia detected) will be demonstrated if the upper limit of a one-sided 97.5% confidence interval around the expected true difference of 0.5% in favour of the control group (15% vs 14.5%) excludes a difference of more than 5%. If the baseline characteristics potentially influencing event rates have a standardized difference of ≥ 0.1, multivariable analysis will be further conducted.

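### The one-year recruitment window of the pilot go/no-go rule starts at study initiation in two sections and at each site's initiation in a third, and 292 falls just short of the stated 15%

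*Protocol article*

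**What the plan says.** The recruitment criterion for moving from the internal pilot to the full trial appears in several places in the protocol article.

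- **Study outcomes**, pilot item (i): randomisation of at least 15% "of full trial sample size (292 participants) within 1 year of study initiation across the participating sites". This is a total over sites, with one clock.
- **Sample size calculation**: at least 15% of the sample within a year, again counted from study initiation. The threshold is justified by the wish to complete the full trial in 5 to 7 years.
- **Abstract, Methods**: a minimum of 15% within 1 year, with no start point named.
- **Data analysis**: a minimum of 292 participants, glossed as more than 15% "of the full trial sample) to be recruited within 1 year of trial initiation at each site". This section also says that the full trial proceeds if the metrics are met and the safety review raises no concern.

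The full sample is stated in the abstract ("The trial is being conducted at 12 centres across Canada, with a total sample size of 1952 persons") and in Sample size calculation ("The estimated sample size to assess non-inferiority of the intervention in the full trial is 1952 persons (976 per group").

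**The concern.** A progression rule has to give one answer on one data set. Here the one-year window has two different starting points. If every site opened on the same day they would coincide. If openings are spread out, a site-specific clock gives each late site a full year of its own and adds these years together, although they end on different calendar dates. A single study clock counts only what has accrued one year after the study began. The second quantity bears directly on the 5-to-7-year rationale; the first describes the rate at sites once they are open.

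Recruitment is the first-listed of the minimum metrics that justify the full trial. If the wording is left as it is, the clock could be chosen after the recruitment figures are known.

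A smaller fault lies in the threshold itself: the count and the percentage do not agree.

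**Working it through.** **Inputs from the article.** Full sample 1952; 12 centres for the trial as a whole; threshold 292, given as at least 15% (Study outcomes) and as more than 15% (Data analysis); one-year window; target duration 5 to 7 years.

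**1. The full sample size reproduces.** The inputs, from Sample size calculation, are a one-sided alpha of 2.5%, power of 80%, a control rate of 15%, an intervention rate of 14.5% and a margin of 5 percentage points, with 1:1 allocation. With unpooled variance:

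n per arm = (1.960 + 0.842)² × (0.15 × 0.85 + 0.145 × 0.855) / (0.05 − 0.005)² = 7.849 × 0.251475 / 0.002025 ≈ 975

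That is 1950 in total against 1952 stated. The denominator of the percentage is therefore sound.

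**2. The threshold.**
- 0.15 × 1952 = 292.8, so 292 is this figure rounded down.
- 292/1952 = 14.96%, below 15%.
- 293/1952 = 15.01%, the smallest whole number that satisfies either percentage.

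**3. What the Data analysis sentence means.** The reference to each site can attach to two things.
- *To the initiation.* The total is 292, and each site's year starts when that site starts. This fits the word order, and it fits the gloss that 292 is about 15% of the full trial sample.
- *To the recruiting.* Every site would need 292. The gloss contradicts this, because 292 is then not a share of the full sample but a count to be multiplied by the number of sites.

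The first reading is the natural one, and it still differs from Study outcomes and Sample size calculation in where the year begins.

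**4. How far apart the two clocks can be.** The article gives no opening dates, so the following rests on assumptions: 12 pilot sites, openings d months apart, an equal and constant rate at each open site, and study initiation taken as the first site's opening.

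Open site-months in the first study year = 144 − 66d (for d up to 1), since the delays add up to (0 + 1 + … + 11) × d = 66d. Take a site-clock total of exactly 292, that is 292/12 = 24.33 per site per year:

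| Spacing d | Open site-months | Total on site clocks | Total on study clock | Share of 1952 |
|---|---|---|---|---|
| 0 (all together) | 144 | 292 | 292 | 14.96% |
| half a month | 111 | 292 | 292 × 111/144 ≈ 225 | 11.5% |
| one month | 78 | 292 | 292 × 78/144 ≈ 158 | 8.1% |

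**5. How wide the band of disagreement is.** Using 293 as the threshold under both clocks, the site-clock rule passes and the study-clock rule fails for site-clock totals from 293 up to, but not reaching, 293 × 144/(144 − 66d):
- half-month spacing: 293 × 144/111 ≈ 380
- one-month spacing: 293 × 144/78 ≈ 541
- simultaneous opening: no band at all

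**6. Relation to the time frame.** At 292 a year throughout, 1952/292 = 6.7 years. With one-month spacing and 292 a year once all sites are open, 1 + (1952 − 158)/292 ≈ 7.1 years. Both figures assume that the rate does not rise after the pilot.

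**The case against.** The strongest reply is that this is loose wording with little consequence. The sentence in Data analysis defines 292 as a share of the whole trial, so nobody applying it would be misled about the total. The clocks differ only if openings are materially staggered, and no opening dates are given, so the effect cannot be sized from the article. A per-site year is also a legitimate estimate of recruitment at open sites. The 6.7 years implied by 292 a year lies inside the stated time frame, and the Discussion describes the pilot as coming before expansion to the complete trial, which could raise the later rate. The percentage slip matters only if exactly 292 people are randomised. Nothing here touches the margin, the power or participant safety.

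Much of this stands. The size of the clock effect is unknown, the rounding is trivial in practice, and the 7.1-year figure is an illustration and not a forecast. A per-site clock could be a reasonable choice if it were the only one stated.

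What does not stand is that the difference is harmless. The article sets two different windows for a criterion on which continuation depends. Under moderate staggering, the totals on which they disagree are not confined to the immediate neighbourhood of 292.

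A reader might go further and infer that Data analysis demands 292 at every site: 292 × 12 = 3504, more than the 1952 in the whole trial, and hence an impossible rule. The documents do not support that. The gloss on the full trial sample contradicts a per-site count, the reference to each site follows directly on initiation, and Study outcomes gives a total across sites. Moreover, 12 is the number of centres in the trial as a whole; the Discussion speaks of a specific set of centres for the pilot without saying how many.

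**Conclusion.** The recruitment criterion is inconsistent as written. Study outcomes and Sample size calculation run the year from study initiation; Data analysis runs it from initiation at each site. With staggered openings the same data can pass one and fail the other. The difference ranges from nothing (all sites open together) to, under the assumed one-a-month opening of 12 sites, 292 on one clock against about 158 on the other. The true size depends on opening dates that the article does not give.

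The threshold is also one participant short: 292 is 14.96% of 1952, so it meets neither the inclusive nor the strict form of 15%. This has no practical bearing on feasibility, but a decision threshold should not have a count and a percentage that disagree.

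The rule is not impossible to meet, and the validity of the full trial's primary analysis is not affected. The case for correcting it is that it decides continuation and the correction costs almost nothing.

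**What to change.** State one criterion, in the same terms, in Study outcomes, Sample size calculation and Data analysis: at least 293 participants (at least 15% of 1952) randomised in total across all participating sites within 1 year of a single study start date. Remove the reference to each site from Data analysis, and use the inclusive sign throughout in place of the strict one.

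The sponsor should define the start date in advance, without reference to the recruitment figures. The article does not favour one definition over another, so the choice is the sponsor's; what matters is that there is only one.

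The cost is a wording change in three sections and one more participant in the threshold. The design, the sample size and the analysis of the full trial are unchanged.

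### The pilot's progression limit for major protocol violations is below 10% in one section and up to 5% in another, so the same pilot result can pass and fail

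*Protocol article*

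**What the plan says.** Three places in the Protocol article bear on this criterion.

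- **Study outcomes** introduces its list as "pilot phase outcomes (minimum metrics to justify full trial" and sets the second item at "< 10% rate of major protocol violations, on a per-patient basis".
- **Data analysis** states "We will accept up to a 5% rate of major protocol violations" among pilot participants. It then makes progression conditional on the limits in that paragraph: "If these metrics are met and there are no safety concerns with the study intervention", where the safety judgement follows review by the Data and Safety Monitoring Committee.
- **Abstract, Methods** speaks of "maintaining ≥ 90–95% rate of protocol adherence and data capture", a single range covering two different measures.

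The pilot size is fixed in Study outcomes: "Randomization of ≥ 15% of full trial sample size (292 participants) within 1 year".

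**The concern.** The two limits concern the same measure, the same participants and the same decision, yet they differ by a factor of two. No section calls one a target and the other a minimum, or sets a zone between them in which the protocol would be amended and the trial continued.

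Protocol adherence is one of the pilot's three stated primary aims (Study objectives), and the pilot decides whether a 1952-person trial is completed. If the observed rate falls between the two limits, the rule gives no answer. Whoever decides could cite either section after seeing the rate. Keeping allocation concealed does not prevent this, because an overall violation rate can be known without unblinding.

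**Working it through.** **Inputs.** Full trial size 1952, or 976 per group (Sample size calculation); pilot size 292 (Study outcomes); limits of below 10% (Study outcomes) and up to 5% (Data analysis). The true violation rate is not given and is varied below as an assumption.

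**Reproducing the plan's own figure.** With detection rates of 15% and 14.5%, a 5-point margin, one-sided 2.5% significance and 80% power:

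n per group = (1.960 + 0.842)² × (0.15 × 0.85 + 0.145 × 0.855) / (0.05 − 0.005)² ≈ 7.849 × 0.2515 / 0.002025 ≈ 975

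That is 1950 in total against 1952 stated, so the sample size reproduces. The pilot size follows from it: 0.15 × 1952 = 292.8, given as 292.

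**Limits as counts out of 292.**

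- Up to 5%: 0.05 × 292 = 14.6. Then 14/292 = 4.79% passes and 15/292 = 5.14% fails, so the maximum is 14.
- Below 10%: 0.10 × 292 = 29.2. Then 29/292 = 9.93% passes and 30/292 = 10.27% fails, so the maximum is 29.
- Counts from 15 to 29 pass under Study outcomes and fail under Data analysis. At 14 or fewer, or 30 or more, the sections agree.

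**Chance of conflicting verdicts.** Let X be the number of participants with a major violation, X ~ Binomial(292, p). The chance of conflict is P(X ≤ 29) − P(X ≤ 14).

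| Assumed true rate p | Passes at ≤ 5% | Passes at < 10% | Conflict |
|---|---|---|---|
| 3% | 0.968 | 1.000 | 0.032 |
| 5% | 0.506 | 1.000 | 0.494 |
| 6% | 0.233 | 0.997 | 0.764 |
| 7% | 0.081 | 0.977 | 0.895 |
| 7.5% | 0.044 | 0.949 | 0.906 |
| 8% | 0.022 | 0.904 | 0.882 |
| 10% | 0.001 | 0.534 | 0.533 |
| 12% | 0.000 | 0.159 | 0.159 |

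Among the rates tabulated, conflict is most likely at 7.5%, and it is unlikely when violations are rare or very common.

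**Comparison with the other pilot criteria.** Loss to follow-up is below 5% in Study outcomes and up to 5% in Data analysis. Missing data on the key variables is below 1% and up to 1%. These pairs differ only exactly at the boundary. The twofold gap is therefore particular to the violation limit and is not a matter of loose inequality signs.

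**The case against.** The strongest objection is that little depends on this. The conflict arises only for observed rates between 5% and 10%. It leaves the full trial's design untouched, and progression also requires a review by a committee whose members are outside the trial's design and conduct. The limits on scope are correct and hold the severity down. The committee review does not remove the problem: in Data analysis it is a safety condition added to the metrics, and it does not say which violation limit applies.

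Three stronger readings are tempting, and the article supports none of them.

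- **That 5% is the intended limit, because it stands beside the decision to proceed.** Study outcomes calls its own list the minimum for progression, so both limits claim the same status. The abstract leans the other way if anything. Its range covers adherence and data capture together, and can be read as about 90% adherence (violations below 10%) with about 95% capture (the below-5% limit for missing non-essential variables). That fits Study outcomes without conflict. It is not decisive, and it also means the abstract should not be read as a blend of the two violation limits.
- **That the looser limit costs the full trial per-protocol power.** This would require every major violator to leave the per-protocol set, equally by arm and with detection rates unchanged, none of which the article states. A threshold applied to about 15% of participants also does not set the violation rate in the full trial.
- **That violations necessarily make the arms alike and so favour non-inferiority.** The article does not define a major violation. Breaches of the biopsy allocation would draw the arms together; breaches of eligibility or minimum withdrawal time need not.

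**Conclusion.** Wrong as written, with moderate severity. One progression criterion carries two incompatible limits with no stated tiering, and at 292 pilot participants every count from 15 to 29 receives opposite verdicts.

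The counts follow directly from the article. The probabilities rest on assumed true rates and on independent violations with a common rate. Across true rates of 3% to 12% the chance of conflict runs from about 3% to about 91%, so no single figure should be taken as the expected one.

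The defect is confined to the decision to continue after the pilot. Sample size, significance level, non-inferiority margin and primary analysis of the full trial are unaffected.

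**What to change.** Before pilot violation data are reviewed, the authors should state which single limit governs and use it in both Study outcomes and Data analysis. If two tiers were meant, they should say so and state what follows from a rate between them. In the abstract, the combined range should be replaced by one figure for adherence and one for data capture. The choice of value belongs to the authors, since the article does not show which was intended.

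The edit is a few words, but the choice has consequences. If the stricter limit is adopted, the pilot becomes materially harder to pass: at an assumed true rate of 5%, the chance of meeting this criterion is about 51% under the 5% limit and close to 100% under the 10% limit; at 7% it is about 8% against 98%. If the looser limit is adopted, the article should no longer say that only 5% is accepted.
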